## **List of Abbreviations**

2MWT – Two Minute Walk Test

4SBT – Four Stage Balance Test

ABC – Activity Balance Confidence

AE – adverse event

APSRA – PROMIS-APSRA, Patient-Reported Outcomes Measurement Information System  
Ability to Participate in Social Roles and Activities

BBS – Berg Balance Scale

CCTV – closed-circuit television

DoD – Department of Defense

FSST – The Four-Square Step Test

HM – high mobility

ISSO – information system security officer

LLA – lower limb amputation

LM – low mobility MVAHCS – Minneapolis Veterans Administration Health Care System

NBWT – Narrowing Beam Walking Test

NSR – non-significant risk

PFE – prosthetic foot emulator

PHI – protected health information

PLUS-M – Prosthetic Limb Users Survey of Mobility

RAC – Regional Amputation Center

SAE – serious adverse event

TAPES-R – Trinity Amputation and Prosthesis Experience (revised scales)

TTA – transtibial amputation (below-knee)

VAPSHCS – Veterans Administration Puget Sound Health Care System

# **Protocol Title: A Prosthetic Foot Test-Drive Strategy for Improving Stability and Falls-Related Outcomes in Veterans with Leg Amputations**

## **1.0 Objectives**

### ***Specific Aim 1: Determine the effects of commercial prosthetic feet of varying stiffness on stability and falls-related outcomes in Veterans with TTA***

*H1.1:* Prosthetic feet with the lowest coronal plane stiffness will correlate with greater self-reported (i.e., Perceived Stability) and biomechanical (i.e., Medial/Lateral Margin of Stability (MOS)) stability outcomes during walking on uneven ground and cross-slopes, as well as greater balance confidence (i.e., ABC), performance-based stability (i.e., NBWT and Four Square Step Test (FSST)), and less activity restriction (i.e., PROMIS Ability to Participate in Social Roles and Activities (APSRA)) after community use.

*H1.2:* Prosthetic feet with the lowest sagittal plane stiffness will correlate with greater self-reported (i.e., Perceived Stability) and biomechanical (i.e., Anterior/Posterior MOS) stability outcomes during walking on inclines, as well as greater balance confidence (i.e., ABC) and stability (i.e., NBWT and FSST), and less activity restriction (i.e., PROMIS APSRA) after community use.

### ***Specific Aim 2: Determine whether a multiaxial prosthetic foot emulator can be used to predict stability and balance-confidence outcomes with corresponding commercial prosthetic feet in Veterans with TTA.***

*H2.1:* Participants' initial perceived stability with each emulated foot will correlate with their perceived stability with the corresponding actual foot at follow-up.

*H2.2:* Participants' initial perceived stability with each emulated foot will correlate with their balance confidence (i.e., ABC) and stability (i.e., NBWT and FSST) in the corresponding actual foot at follow-up.

### ***Specific Aim 3: Determine whether a brief trial of commercial prosthetic feet can predict longer-term stability and balance-confidence outcomes in Veterans with TTA.***

*H3.1:* Participants' initial perceived stability with each actual foot (relative to other feet) will correlate with their perceived stability with the corresponding foot at follow-up.

H3.2: Participants' initial perceived stability with each actual foot will correlate with their balance confidence (i.e., ABC) and stability (i.e., NBWT and FSST) in the corresponding foot at follow-up.

## 2.0 Study Procedures

### 2.1 Study Design

#### *Study Population*

Participants will be men and women, age 18 or over, with a unilateral TTA that have been fit with a prosthesis and use it on a regular basis (full inclusion/exclusion criteria are listed below). Participants will be recruited at two sites: VA Puget Sound and Minneapolis VA. We will conduct a participant-blinded cross-over study with repeated measurements. Data collection methods will be identical at both sites. Participants will walk in the laboratory with the PFE and with corresponding/matched, commercial prosthetic feet under various walking conditions (e.g. level ground, incline, cross slopes, uneven ground). Participants will then wear each of the commercial feet at home and in the community for one-week periods. Participants will then return to the laboratory for follow-up visits after each one-week trial period to assess foot preference, stiffness perception, balance confidence, activity restrictions, stability, and falls-related outcomes in order to determine whether the PFE and/or a brief trial of commercial feet in the laboratory are able to predict mobility, stability, and falls-related outcomes after one week of use in the home and community setting.

No exclusions based on sex, race, or ethnic status will be applied.

| Study Groups and sites (enrollment)               |                  |
|----------------------------------------------------------|------------------|
| Seattle VA: Participants with transtibial amputation     | up to 50         |
| Minneapolis VA: Participants with transtibial amputation | up to 50         |
| Total VA sites                                    | up to 100 |

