**Physical risk management:** These risks will be minimized by providing frequent rest breaks during study sessions, providing prosthetic foot acclimation periods during study sessions, fitting participants with commonly-prescribed commercially available prosthetic feet that are specific to their mobility level (low or high), conducting walking tests at participants’ self-selected speeds, and having experienced certified prosthetists conduct all prosthetic fittings. Since participants will have a chance to wear each of the commercially available feet for at least an hour in the laboratory setting with an optimized alignment, we do not expect any problems to arise during the one week at home portions of the study. However, if a participant becomes uncomfortable with the study foot for any reason during the course of the study, they will be provided the opportunity to meet with our study prosthetist who will assess the study foot and alignment and make adjustments as necessary. If not feasible to visit the study prosthetist, the study prosthetist can recommend that the participant see their own, or a local prosthetist, for the alignment assessment and change. A note will be made by the study prosthetist to document this necessity. If a participant is not comfortable wearing any of the study prosthetic feet, they can opt out and we will replace the study foot with their originally prescribed prosthetic foot and study participation can be terminated as per participant request at any time.

To minimize the risks of falls or injury, the treadmills are equipped with safety handrails, and emergency stop capabilities. Participants will also be offered the option to be fit with additional supports (e.g., safety harness that is attached to the ceiling of the lab or a gait belt) while performing walking tests on the treadmill(s) while using the prosthetic foot emulator or the commercially available study feet. If a participant declines to be fitted with the extra safety equipment but appears unsteady or experiences a fall, we will request that they wear it if they wish to continue in the study. During the balance tests, two study personnel will also be present and stay close to the participant to ensure safety during these activities. Participants will also be able to skip any or all of the performance-based clinical tests should they not feel comfortable completing them. This will not disqualify them from participating in the rest of the study.

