2. The Four-Square Step Test (FSST): The FSST is a clinical outcome measure designed to assess dynamic balance. Participants are asked to step quickly in a 4-step pattern (i.e., forward, laterally, and backward) over canes (e.g., PVC piping) laid on the floor as per standard administration of the test. Participants complete the test twice while wearing their prescribed prosthetic foot, and the fastest of the two times required to complete the test is recorded. The FSST, including instructions, a practice trial, and the two timed trials, takes no more than 5 minutes to complete.
3. 4 Stage Balance Test (4SBT): The 4SBT is a performance-based test of static balance. There are up to four standing positions that get progressively more challenging to maintain for 10 seconds without moving their feet or needing support. The four positions are: feet side-by-side, placing instep of one shoe so it is touching the big toe of the other shoe; tandem stance of one shoe in front of the other with heel touching toe; and standing on one foot. Each position is described and demonstrated to the participant. Then, the participant may be guided and supported into assuming each correct position. When the participant is steady, they are timed to see how long they can maintain the position, but with close guarding ready to assist them if they should lose their balance and need to take a step. If the participant can hold a position for 10 seconds without moving their feet or needing support, they proceed to the next position. Participants are scored based on how many of the four stages they can safely complete.
4. Narrowing Beam Walking Test (NBWT): The NBWT is a performance-based test of balance for lower limb prosthesis users. It is comprised of four sets of low-to-the ground (i.e., approximately 4cm) beams that become increasingly narrow in width. Two practice trials and then three measured trials are performed with the distance walked on the beam averaged to produce a final score. The NBWT takes 3-5 minutes to complete. All trials will be done while the participant is wearing their prescribed prosthetic foot.
5. The L Test of Functional Mobility (L Test): The L test is a clinical measure designed to assess functional mobility. Participants will be asked to rise from a chair, walk 3 meters, turn at ninety degrees, walk 4 more meters and turn around, walk 4 meters, turn ninety degrees,

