The study research prosthetist will fit participants with a robotic ankle-foot prosthesis (the multiaxial prosthetic foot emulator, PFE). The PFE will be attached to participants' current prosthetic socket in the same way that a regular prosthetic foot would be attached. The PFE can be programmed to operate in different modes that mimic the mechanical properties of different commercially available prosthetic feet. For this study, the PFE will be programmed with 5 foot modes – 3 high mobility feet and 3 low mobility feet (one foot mode is shared between high and low mobility groups). Designated research staff will use the computer software interface to switch the PFE between different foot modes and adjust hardware on the foot (e.g., adding small brass weights to mimic the weight of the corresponding prosthetic feet). Changing out the physical foot is not necessary. After participants are fitted with the PFE, we will give them time to

walk at their comfortable speed on the treadmill again while using the PFE in up to 3 different modes (3 high mobility vs. 3 low mobility modes depending on their 2MWT; see details above). Participants can choose to adjust their walking speed while walking with the PFE by increasing and/or decreasing the speed on the treadmill at any time. This will allow the participants to practice walking with the PFE and we will assess their walking ability to confirm whether the participant is a good fit for the study. Adjustments may be made to the PFE hardware or software settings in order to optimize the walking performance for each participant. If participants are not able to feel confident and stable on one or more of the modes, we will stop the session. We will also give participants time to rest at any point, and each time we switch foot modes. Participants may also be offered an opportunity to practice walking with the 3 different commercially available actual study feet.

At the end of the study visit, the prosthetist will refit the participants' prescribed prosthetic foot. The next study visit will be scheduled and a reminder slip can be given to the participant.

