#### Visit 2: Randomization & First Initial Testing Visit – Emulator or Actual Feet (approximately 3 hours)

Based on the result of the 2MWT completed during Visit 1, participants have been assigned to the low mobility group (LM) or the high mobility group (HM) (see details above). At this visit, within each group (LM and HM) participants will be randomized to test either the PFE in the 3 foot modes for their group (LM vs. HM) or the 3 actual corresponding prosthetic feet for their group. Once randomized to PFE or actual feet, the order in which the different modes and actual feet will be tested will also be randomized; participants will be blinded to all PFE modes and actual foot conditions until the completion of the study. At visit 3 they will be tested under the other condition (e.g., if randomized to PFE testing during Visit 2, the participant would undergo testing with the corresponding actual feet during Visit 3).

The research prosthetist will fit participants with the assigned prosthetic feet (PFE or actual feet); participants will use their own prosthetic socket, interface and prosthetic suspension system. Participants will be asked to walk at their chosen comfortable speed on the treadmill while using the first randomly assigned PFE mode or actual foot until they feel comfortable. Adjustments may be made to the hardware or software settings in order to optimize the walking performance and comfort for each participant, if needed. If participants are not able to feel confident and stable on one or more of the PFE modes or on one of the actual feet, we will stop the session. We will also give participants time to rest at any point, and at every instance between switching modes or switching between actual feet. Participants will be able to take rest breaks at any time during the testing procedures and may choose to opt out of any of the tests at any time.

Please note: Participants will be allowed to hold onto the safety bars at any time on the treadmill(s) if needed in order to keep their balance. They will also be offered the option of using additional supports (e.g., gait belt, overhead safety harness) while walking on the treadmill(s) throughout the study.

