### Visit 3: Second Initial Testing Visit – Emulator or Actual Feet (approximately 3 hours)

At this visit participants will be asked to repeat the study procedures described above in Visit 2; they will complete the procedures using the equipment (PFE or actual feet) that they did not use during Visit 2 (based on randomization as described above).

At the end of this visit, the prosthetist will fit participants with one of the three actual feet that they used earlier; foot order will be randomized again and participants will remain blinded to foot condition (lightweight fabric will be secured around any potentially identifying features of the prosthetic foot using zip ties). Participants will wear the assigned study prosthetic foot (connected to their prescribed socket) for the next one week at home and in the community. Participants will be scheduled to return for a follow-up visit after this one-week period. Designated study staff will store the participants' prescribed prosthetic foot in a designated, secured cabinet within a locked office until they have completed the study or choose to stop their participation. Participants will be instructed to contact us if they have any concerns or discomfort associated with their prosthetic limb. If needed, participants can come in for prosthetic alignment adjustments during the 1 week in home/community test window. Alternatively, participants may also see their own prosthetist for adjustments, if needed, during the test window. In this case, study staff will make note of the necessity for the change and the clinic that the participant visited.

Note that prosthetic alignment will be optimized under all foot conditions.

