### Visits 4, 5 and 6: Follow-up Testing Visits (up to 4 hours each)

During each of these visits, participants will be asked to complete a survey that includes questions about their preference, stability, perceived foot stiffness, satisfaction, balance, activity restrictions, fear of falling, and mobility while using the study assigned prosthetic foot that they wore for the past week. During each of these visits, participants will be asked to repeat some of the performance-based balance-related outcome measures (i.e., FSST, 4SBT, NBWT, L test) (as described under Visit 1, with the only difference being that participants will be wearing the respective study prosthetic foot during visits 4, 5, and 6).

Furthermore, during these visits, a 16-camera motion capture system (Vicon Motion Systems Ltd., Oxford, UK) or an IMU system (XSens, Movella Inc., Henderson, NV, USA) may be used to collect positional data, using the same procedures described above in visits 2-3. Up to eighty reflective markers, or up to twenty-five IMUs, will be placed on anatomical locations (e.g., arms, legs, torso) and corresponding measurements will be taken (e.g., leg length, ankle width) according to the Vicon Full Body Plug-In Gait method. No data will be shared with Vicon Motion Systems Ltd. or Movella Inc. Participants may be asked to repeat some of the previous study procedures (i.e., walking conditions) while biomechanics data is being collected. Specifically, they may be asked to repeat

some of the previous study activities, including standing and walking trials overground and on the level, inclined, cross-slope, and uneven treadmill conditions (see details above, depending on their LM or HM group assignment) at their self-selected comfortable, slow, and fast walking speeds using the study foot that they have accommodated to following their one-week at home trial. As is standard for gait biomechanical data collection, the infrared motion capture cameras will collect marker coordinate data during walking if using the marker-based motion capture system. Embedded force platforms may also be used to collect synchronized ground reaction force data. The participants will be allowed to rest as much as needed between or during study activities.

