At the end of Visits 4 and 5, the prosthetist will fit participants with one of the other remaining prosthetic feet (based on their randomized foot order and participants will remain blinded to foot condition). Participants will wear the assigned prosthetic foot (connected to their prescribed socket) for the next one week at home and in the community. Again, participants will be scheduled to return for a follow-up visit after one week. Participants will be reminded to contact us if they have any concerns or discomfort associated with their prosthetic limb. If needed, participants can come in for prosthetic alignment adjustments during the one-week in home/community test window. Should it not be feasible for the participant to come in to a study site (e.g., VAPSHCS) for alignment adjustments, study staff can recommend that the participant see their local prosthetist for any necessary changes. In this case, study staff will make note of the necessity for the change and the clinic that the participant visited.

Testing procedures will be repeated again at Visit 6. At the end of Visit 6, the prosthetist will re-fit the participants' prescribed prosthetic foot, which will conclude the testing sessions.

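### Blinding covers participants only: nothing keeps the foot's identity from staff who score the balance tests, and the participants' cover is specified only for the take-home fitting

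*Protocol*

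**What the plan says.** **Who is blinded.** Protocol 2.1 (Study Population): "We will conduct a participant-blinded cross-over study with repeated measurements". Section 2.5, Visit 2, sets the scope: "participants will be blinded to all PFE modes and actual foot conditions until the completion of the study". The text on Visits 4, 5 and 6 continues it: the next foot is fitted "based on their randomized foot order and participants will remain blinded to foot condition". The protocol masks no assessor, prosthetist or data processor.

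**How participants are blinded.** One method is described, in a parenthesis on the take-home fitting at the end of Visit 3: "lightweight fabric will be secured around any potentially identifying features of the prosthetic foot using zip ties".

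**Visit 1.** Walking on the emulator is part of the visit for eligible participants. For the commercial feet the text reads: "Participants may also be offered an opportunity to practice walking with the 3 different commercially available actual study feet". It mentions no cover and gives no rule for who is offered the practice.

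**What is scored, and by whom.** At Visits 4-6 "participants will be asked to repeat some of the performance-based balance-related outcome measures (i.e., FSST, 4SBT, NBWT, L test"), on the study foot worn for the past week. Under Visit 1, NBWT is the mean distance over three measured trials, and for FSST "the fastest of the two times required to complete the test is recorded". The scorer is not named and is not separated from the prosthetist who fits the foot. Risks and Risk Management adds: "During the balance tests, two study personnel will also be present and stay close to the participant".

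**The concern.** H1.1 and H1.2 predict that the feet with the lowest stiffness go with better stability, and both name NBWT and FSST. The two tests are also follow-up outcomes in H2.2 and H3.2. They yield a distance and a time, but people administer them. Someone decides when a beam walk has ended, works the stopwatch, accepts or repeats an FSST attempt, guards the participant and gives encouragement. A staff member who knows both the foot and the hypothesis can shift the result in the predicted direction without intending to. The analysis cannot remove such a shift, because it is aligned with foot, the factor under test.

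On the participant side, Perceived Stability and ABC are self-reports, so they depend on the blind. A blind to every actual foot until study end needs a method wherever an actual foot is worn. The protocol gives one for the take-home fitting only.

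The optional Visit 1 practice raises a separate matter. The initial actual-foot rating in Aim 3 is a first exposure for some participants and a second for others, with no rule and no record of which. That holds even if every foot is covered.

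**Working it through.** The point rests on the text, not on a number. The passages side by side:

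| Stage | Actual feet worn? | Participant blind stated? | Cover stated? | Scorer masked? |
|---|---|---|---|---|
| Visit 1, optional practice | yes, up to three | not at this visit; Visit 2 text covers all actual feet | no | no balance test on study feet |
| Visits 2-3, laboratory testing | yes, at one of the two | yes | no | not stated |
| End of Visit 3, take-home fitting | yes | yes | yes | not applicable |
| Visits 4-6, balance tests | yes | yes | carried over by implication | not stated |

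Masking the scorer at Visits 4-6 is practicable. The foot under test was fitted at the end of the preceding visit, and the next foot is fitted at the end of the current one. No fitting has to take place before the tests, so the scorer need not see the foot uncovered or hold the sequence.

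**Does the point touch the sample size?** Inputs from section 2.6 (Power Analysis): NBWT within-participant SD 2.7 ft, difference 2 ft in one pair, type 1 error .01; MOS within-participant SD 1.0 cm, differences 1 cm and 0.7 cm. With three feet per participant, means (0, 0, d) and an overall 2-df test of foot, the noncentrality is λ = n·Σ(μⱼ − μ̄)²/SD² = n·(2/3)d²/SD², with 2 and 2(n − 1) degrees of freedom.

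- NBWT, n = 40: λ = 40 × 2.667/7.29 = 14.6, power 79.6% (stated 81%).
- NBWT, n = 50: λ = 50 × 2.667/7.29 = 18.3, power 90.0% (stated 91%).
- MOS 1 cm, n = 40: λ = 40 × 0.667/1 = 26.7, power 98.2% (stated 98%).
- MOS 0.7 cm, n = 50: λ = 50 × 0.327/1 = 16.3, power 85.5% (stated 87%).

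Simulation of 20,000 data sets per case with a 2-df chi-square cut-off gives 82.0%, 91.2%, 98.5% and 87.1%. The stated figures reproduce, and masking enters none of them.

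**What a scoring bias would do, as an assumption only.** The protocol gives no bias size. Suppose scoring favours one foot by b ft on the averaged NBWT and there is no true difference. With 60 × 0.8 = 48 completers, the standard error of a pairwise difference is 2.7 × √(2/48) = 0.551 ft. The chance of a two-sided pairwise rejection at .01 is P(|t′| > t₀.₉₉₅) on 2 × 47 = 94 df, with noncentrality b/0.551:

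| Assumed b (ft) | b/0.551 | False-positive rate (nominal .01) |
|---|---|---|
| 0.25 | 0.45 | .018 |
| 0.50 | 0.91 | .046 |
| 0.75 | 1.36 | .108 |
| 1.00 | 1.81 | .214 |

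This shows how sensitive the test is to a bias of given size. It is not evidence that a bias exists.

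**The case against.** The best defence is that participant-only blinding is openly declared and contradicts nothing. NBWT and FSST are a distance and a time with set trial rules, so the room for bias is small. Nothing says that the scorer knows the foot. All of that is true. It limits the likely size of the problem, but the plan still permits an informed scorer where a masked one could be used.

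Several stronger readings are tempting, and the documents do not support them:

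- *Visit 1 practice is done on visible feet.* The text does not say so. The Visit 2 statement covers all actual feet, and the Visit 3 text says that participants remain blinded. The cover is unstated, not absent.
- *Seeing a foot at Visit 1 breaks the blind.* Not by itself. Foot order is randomized at Visit 2 and again for the take-home weeks, and identifying features are then covered. The participant would still have to match a covered foot to one seen earlier. An inflated Aim 3 association through such recognition is conjecture.
- *The balance tests are the only follow-up outcomes that are not self-reported.* MOS may also be collected at Visits 4-6 from motion capture or inertial sensors.
- *A particular share of the 2 ft difference is at risk.* Any such share comes from an assumed bias.

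Two further objections stand in part. Participants walk on each foot at Visit 2 or 3 until comfortable before rating it. That softens the unequal exposure but leaves it unrecorded. The two staff at the balance tests are there for safety, so the site must confirm that one of them can also score.

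**Conclusion.** The point holds as a gap in the stated masking. The protocol does not keep the foot's identity from those who administer and score the Visit 4-6 performance tests. It states a masking method for one fitting although the blind covers every foot condition, and it leaves actual-foot exposure before the Aim 3 initial rating uneven. Assessor masking and use of the cover are matters of conduct that belong in the protocol, and analysis cannot repair them afterwards.

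The size of any bias is unknown, and the table of assumed biases carries no evidence about it. Sample size, type 1 error and stated power are unchanged. The change is worth making because it reduces a possible bias at little cost. The gap does not invalidate the trial. The conclusion assumes that no separate, unseen procedure already masks the scorer or requires the cover throughout.

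**What to change.** 1. **Scorer.** Let only the fitting prosthetist hold the foot sequence. Have one of the study staff already present, who is not involved in fitting and is not told the foot, instruct and score NBWT, FSST, 4SBT and L Test with the cover on. Process MOS, where collected, by coded foot.
2. **Cover.** State that the existing fabric cover is used whenever an actual foot is worn in front of the participant or the scorer, at Visits 1-6. Outside prosthetists may adjust a foot and the protocol cannot bind them, so have study staff check the cover at the next visit after any such adjustment.
3. **Visit 1.** Drop the optional practice with the actual feet. If it is kept, cover the feet and record who had it.

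**Cost.** Protocol wording, some cover handling and a division of tasks among existing staff; no added procedure, participant or visit. Giving covered practice to everyone would also equalise exposure, but it would add fittings to a visit of about three hours, so dropping it is simpler. Masking will remain imperfect: fabric does not hide weight, feel or gait, and scorers will see the same few feet repeatedly.
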